## Abstract

This study aims to evaluate the effects of a Walking Football (WF) programme on physical fitness, body composition, health-related quality of life (QoL), and happiness in men and women over 60 years. WF is proposed as a safe and accessible activity to counteract physical inactivity and chronic conditions in ageing populations. A randomized controlled trial will be conducted with 120 participants (both sexes), assigned to either an experimental group (WF intervention) or a wait-list control group. The six-month intervention includes bi-weekly sessions with skills training, match simulations, and fitness exercises. Assessments will be performed at baseline, 3 months, and 6 months. Primary outcome measures will be: body composition (weight, BMI, fat and lean mass), muscular strength, aerobic endurance, agility, range of motion, and subjective well-being (QoL and happiness scales). Linear mixed-effects models and ANCOVA will be used to analyse the data. It is expected that WF will lead to improvements in physical and mental health, contributing to active ageing. This study may also support WF as a tool for social inclusion and well-being in older adults.

## 1. Introduction

The average age of the global population is getting higher [1]. As a consequence, ageing can lead to problems of health, social and emotional well-being, as there is an increased incidence of cardiovascular diseases, metabolic and cognitive disorders [2], loss of both muscle mass and muscle quality [3,4] as well as bone mass [3,5], and chronic inflammation [6]. In the coming years, the number of older people is expected to increase, which will lead to a higher demand for health services [7]. This increase poses fiscal and social challenges for governments, especially as older people are more likely to suffer from chronic diseases compared to the younger population [1]. In addition, happiness is crucial for health and QoL, especially among older adults who often face significant life changes that can impact their well-being [8]. Older adults often experience significant life changes, such as losing a spouse, health issues, isolation, and a loss of purpose, which can greatly impact their happiness [8].

In general, in the case of Western societies, there are difficulties in promoting active and healthy ageing [7]. The social complication lies in the physical activity (PA) levels of this population. As people age, the frequency of participation in regular PA decreases [9,10,11] and thus increases levels of physical inactivity and sedentary lifestyles, defined as sitting or lying down for prolonged periods of time [12,13]. Adults mainly do not meet the recommended levels of PA [9,11,14,15]. Such inactivity, coupled with the diseases of old age, increases the likelihood of developing chronic non-communicable diseases [16], leading to a decline in mental health [9] and increasing the risk of mortality from any cause [10]. The management of the quality of life (QoL) of this population is a complex and difficult problem to address due to its multitude of possible factors. Therefore, it is essential to promote PA to maintain a good QoL. PA and exercise have been shown to have a positive effect on some of the negative factors of ageing [17,18,19,20].

Related to the common early problems of ageing, PA has been shown to be a key element in reducing the risk of chronic diseases and improving overall health, with physiological benefits [17] and psychological [18], as well as improving memory capacity [21]. Within these psychological benefits, it is important to highlight the positive relationship between PA and happiness [22]. Just 10 min of PA a week can increase happiness levels [23].

In view of the major problem of physical inactivity in this population, there is a need for solutions and/or ideas to increase participation levels. One possible way to encourage the adoption of increased PA is through participation in sporting activities [24,25]. Traditional interventions, such as strength training and multicomponent exercise programs, have demonstrated efficacy in enhancing muscle strength, balance, reducing fall risk, better physical fitness, and ability to perform daily tasks among older adults [26,27]. Nevertheless, such programmes may not invariably engender long-term adherence, due to factors such as diminished engagement and constrained social interaction [28]. It is evident that team-based sports have the potential to serve as a particularly engaging form of PA for older adults [25], given their social and physical benefits [29]. However, many traditional sports pose challenges in this age group due to their intensity and the risk of injury. This has resulted in the creation of adapted versions that maintain the fundamental components of the sport while mitigating risk. An exemplar of this is Walking Football (WF).

In this sense, conventional football is one of the most popular sports in the world [30,31], which could be interesting to develop in this population to increase PA levels. In the literature, we can find articles that defend the practice of football as medicine [32,33]. It is fun, social and improves metabolic, cardiovascular and musculoskeletal fitness in different age populations [33,34,35], in addition to preventing falls and fractures [34]. Unfortunately, in older adults, the physical demands of playing some sports such as football can be an obstacle to participation. Thus, adapted sports, which modify various aspects of the conventional sporting structure in order to facilitate the participation of any person, can play a crucial role [36]. For this reason, in recent years a more accessible form of the sport, called WF, has been developed [37]. Its origins date back to 1932 in England [38]. This sport has gained popularity in Europe [39] and new clubs, teams and competitive leagues have also been established in North America and Southeast Asia [37,39], expanding throughout the world [24].

The WF is perfect for those who wish to participate in a team sport and have the physical ability to perform moderate and/or intense PA, but cannot, should not or do not want to run, among other variations of traditional football rules [39]. The main objective of this adaptation is to create a sporty, safer and therefore more accessible and attractive variant for older people [37], but it is also used for initiation, rehabilitation and/or for people who have mobility limitations [24]. It is mainly gaining popularity in the 50 and older population as a lower intensity and safer sport than traditional football [40,41,42].

The scientific literature on the effect of PA on health is abundant, however, research is more limited in sports and specific types of exercise for the adult population [43]. As it is an emerging sport, research is still scarce and with diverse methodologies [24]. However, early studies of WF demonstrate cardio-vascular health benefits [37,39], bone health [37] and improvements in body composition [40,42,44], as well as psychosocial improvements [45]. The majority of extant studies have focused on male subjects [24], there is only one of exclusively women with an average age of 40 years [39] and the others with less than 50% participation of women over 55 [24]. It is crucial to consider the differences between the sexes in order to achieve a comprehensive understanding of the subject. Preliminary data suggest that although men tend to play for longer durations, both sexes experience comparable internal load demands during WF sessions, indicating similar physiological responses to effort [46]. Furthermore, participants of both sexes have highlighted WF as a beneficial activity for maintaining physical and cognitive health, fostering social connections, and reinforcing a sense of community and mutual support [47]. However, no study compares the differences between women and men in relation to QoL and happiness.

Therefore, the aim of this study is to present a research protocol to evaluate the effects of a WF programme on fitness, body composition, health-related QoL and happiness in people over 60 years of age.

## 2. Materials and Methods

### 2.1. Study Design

This study will adhere to the CONSORT (Consolidated Standards of Reporting Trials) guidelines for randomized controlled trials, ensuring methodological rigor and transparency throughout the research process [48]. The design will consist of a randomized controlled trial featuring a 6-month intervention phase. Participants will be randomly assigned to either the intervention group, which will engage in the WF program, or a group that will not receive the intervention (Figure 1). Assessments will be conducted at three key time points: baseline (prior to the intervention), mid-intervention (at three months), and post-intervention (at the end of the 6-month program). This structured approach will facilitate a comprehensive evaluation of the intervention’s effectiveness, allowing for the analysis of changes in health metrics and overall well-being over time. By employing this rigorous design, the study aims to provide robust evidence regarding the impact of WF on the targeted population.

### 2.2. Ethics Approval

Ethical approval for this study was obtained from the Bioethics and Biosafety Committee of the University of Extremadura (149/2022). This ensures that the research adheres to the highest ethical standards, prioritizing the welfare and rights of all participants involved. In addition to institutional approval, the study protocol has been registered with the Australian New Zealand Clinical Trials Registry (ANZCTR) under the registration number ACTRN12624000149561. This registration serves to enhance transparency and accountability in the research process, allowing for public access to the study’s details and methodology. The registration can be accessed at https://www.anzctr.org.au/Default.aspx (accessed on 17 October 2024). By securing both ethical approval and trial registration, the study aims to uphold the principles of ethical research conduct, ensuring that participant safety and informed consent are prioritized throughout the duration of the trial. This commitment to ethical standards is essential for fostering trust and integrity in the research community.

### 2.3. Sample Size

To determine the necessary sample size for this study, an a priori power analysis was performed using G*Power^TM^ software 3.1. [www.gpower.hhu.de (accessed on 20 January 2025)]. The analysis was based on a mixed ANOVA model (within-between interaction), which is commonly used in studies with repeated measures involving multiple groups. Using an alpha level (α) of 0.05 and a desired power (1−β error probability) of 0.80, the analysis revealed that a sample size of 48 participants would be sufficient to detect statistically significant effects. The study will account for an expected loss to follow-up of approximately 25% in the sample size calculation [49]. A total of 120 participants, 60 women and 60 men, will be randomly allocated to either the experimental group (EG) (*n* = 60) or the wait-list control group (CG) (*n* = 60).

### 2.4. Randomisation and Blinding

Participants will be randomly assigned in a 1:1 ratio to either the EG, which will receive the WF training, or the CG, will continue with their usual daily life (Figure 1). To ensure the integrity of the randomization process, a member of the research team who is not directly involved in the trial will generate a simple randomization sequence utilizing Research Randomizer software (version 4.0; accessible at http://www.randomizer.org, last accessed on 31 January 2025) [50].

The details of the group assignments will be securely stored in a password-protected file to maintain confidentiality and prevent any potential bias. Furthermore, during the data analysis phase, researchers will remain blinded to the group allocations, meaning they will not know whether participants belong to the EG or the CG. This blinding process is crucial for minimizing bias and ensuring that the outcomes are evaluated objectively, thereby enhancing the validity of the study’s findings.

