To effectively manage exercise intensity, the sessions will utilize a perceived exertion ratio based on the OMNI 10-point scale [52,54]. This scale ranges from 0, indicating extremely easy exertion, to 10, representing extremely difficult exertion [57]. This subjective measure allows participants to self-regulate their intensity levels, categorizing exertion as light (3–4 points), moderate (5–6 points), vigorous (7–8 points), and maximum (9–10) [57]. This approach not only enhances individual engagement but also ensures that participants can tailor their efforts according to their personal fitness levels and comfort. Throughout the intervention, the intensity of the sessions will progressively increase in accordance with participants’ physical adaptation (Table 1). This is reflected in the planned OMNI scale scores, which are expected to range from moderate (3–4) to moderate-to-high levels (7–8) in the final stages of the programme. This gradual increase is designed to ensure safety, optimise physical improvements, and promote adherence among older adults.

The structure of the session can be found in Table 2. Each intervention session will commence with a structured warm-up, which is divided into two distinct components. The first component is a general warm-up that emphasizes joint mobility exercises and global movements to prepare the body for PA [51]. The second component is more specific [51], incorporating analytical exercises that are commonly utilized in football, such as lateral displacements and changes of direction. Following the warm-up, participants will engage in a traditional match, which may be supplemented with technical and tactical football exercises tailored to the specific phase of the program being implemented.

Participants will be assigned to teams to ensure a balanced distribution. Efforts will be made to achieve an approximately 50% balance of men and women. A similar distribution will be used among the fastest persons, based on the results of the future tests shown in Table 3 (Brisk Walk test). The session will conclude with a cool-down phase that includes relaxation and range of motion exercises, aimed at facilitating recovery and promoting a return to baseline physiological states [51].

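### Simple randomisation does not guarantee the stated 60/60 arms, nor a balance of women and men between them

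*Protocol article*

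**What the plan says.** Section 2.3 (Sample Size) gives both the sex composition and the arm sizes as fixed numbers: "A total of 120 participants, 60 women and 60 men, will be randomly allocated" to an experimental group of 60 "or the wait-list control group (CG) (*n* = 60").

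Section 2.4 (Randomisation and Blinding) gives the ratio, "Participants will be randomly assigned in a 1:1 ratio to either the EG" or the control group, and the method: a team member not otherwise involved in the trial "will generate a simple randomization sequence utilizing Research Randomizer software". No section mentions blocks, strata or minimisation.

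Section 2.9 (Statistical Analysis) handles sex in one of its two models. The ANCOVA adjusts for the baseline value and names age and sex as examples of further covariates. The linear mixed model has group, time and their interaction as fixed effects and a random intercept per participant; sex is not listed. Section 2.9 also plans post hoc comparisons between groups at the separate time points.

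Section 2.7 (Intervention) adds an aim for the teams inside the experimental group: "Efforts will be made to achieve an approximately 50% balance of men and women".

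**The concern.** The two sections describe different procedures. A simple sequence assigns each person independently of the others, so arm sizes and the sex split are random. Fixed arms of 60 require some restriction on the sequence. One of the two statements therefore needs correcting.

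Sex is the natural factor to restrict on, for reasons the article itself supplies:

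- The sample is composed as half women and half men, and sex is known before allocation.
- The Introduction calls it crucial to consider differences between the sexes, and points out that women and men have not been compared on quality of life and happiness.
- The Discussion reports that women keep a greater range of motion than men, and range of motion is one of the outcomes.

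The plan equalises the sexes overall and then leaves their split between arms to chance. At stake are the arm sizes a reader expects to see, and the interpretation of any between-group comparison that does not adjust for sex.

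**Working it through.** **Inputs.** N = 120, with 60 women and 60 men, and arms of 60/60 (Section 2.3). Ratio 1:1 and a simple sequence (Section 2.4). The size of any sex difference on an outcome is not given, so a range is assumed in step 5.

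**1. The stated arm size.** 120 × 1/2 = 60. The figure is reproduced, but as an expected value.

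**2. Arm sizes under a simple sequence.** The experimental arm has size X ~ Binomial(120, 0.5), with SD = √(120 × 0.25) = 5.5.

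- P(X = 60) = 0.073
- P(X ≤ 55 or X ≥ 65), so that the arms differ by 10 or more = 0.411
- 95% range: 49 to 71

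**3. Sex under a simple sequence.** Women and men in the experimental arm are independent, W ~ Binomial(60, 0.5) and M ~ Binomial(60, 0.5). The difference in the share of women is |W/(W+M) − (60−W)/(120−W−M)|. Exact enumeration over all W and M gives:

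- P(difference ≥ 10 percentage points) = 0.315
- P(difference ≥ 15 percentage points) = 0.120
- P(30 women and 30 men in each arm) = 0.1026² = 0.0105

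**4. Sex if the arm totals are forced to 60/60 without strata.** W ~ Hypergeometric(120, 60, 60).

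- P(W = 30) = 0.145
- P(W ≤ 26 or W ≥ 34), a 26/34 split or worse = 0.201
- 95% range: 25 to 35

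**5. Effect on estimates.** Let an outcome differ between the sexes by γ SD at every visit, and let the share of women differ between arms by Δ.

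- The unadjusted group difference at one visit shifts by γ × Δ. With Δ = 0.10 and assumed γ = 0.5, 1.0 or 1.5, the shift is 0.05, 0.10 or 0.15 SD.
- The difference between groups in change from baseline shifts by γΔ − γΔ = 0. The group × time term measures this contrast, so a constant sex offset drops out of it. Only a sex difference in change over time would remain.

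**6. Power cost of unequal arms.** Efficiency relative to 60/60 is 4·n₁·n₂/120².

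- 55/65: 4 × 55 × 65 / 14,400 = 0.993
- 49/71: 4 × 49 × 71 / 14,400 = 0.966

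For a two-group comparison of means set to have power 0.800 at 60/60 (standardised difference 0.5115, an assumption made only to set the scale), power becomes 0.797 and 0.786.

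**7. Precision within one sex.** A split of 22/38 among the 60 women, the edge of the 95% range in step 3, has efficiency 4 × 22 × 38 / 3,600 = 0.929 relative to 30/30.

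**The case against.** The strongest reply is that simple randomisation of 120 people is valid and unbiased, that 60/60 is its expected result under 1:1, and that even an unlucky split costs almost no power. All of that stands. It limits the consequence but does not make the two sections agree.

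A second reply is that the software may have been used to draw a fixed 60 out of 120. The arm sizes in Section 2.3 would then be right, but the word simple in Section 2.4 would be wrong, and step 4 shows that sex would still be left to chance.

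A reader might also infer more than the article supports:

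- **That the stated arms cannot occur.** They can, about 7% of the time. The correct statement is that they are not guaranteed.
- **That the mixed model's intervention effect is biased because it has no sex term.** Baseline is one of its time points, so a constant sex difference leaves the group × time contrast (step 5). The ANCOVA adjusts for baseline and names sex, although only as an example of a covariate.
- **That the mixed-sex team plan fails.** Section 2.7 promises only an effort towards an approximate balance, within one arm, in teams re-formed from whoever attends. The article sets no sex target per arm.
- **That the sex-specific reliabilities in Section 2.8 show different means for women and men.** They describe repeatability. Only the remark on range of motion speaks to a difference in level.

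**Conclusion.** The mismatch between Sections 2.3 and 2.4 is real and rests on the article's own words and exact probabilities: 7% for 60/60, 0.315 for a gap of 10 points or more in the share of women, and 20% for a 26/34 split or worse among women if the totals are forced equal. These figures assume that simple has its usual meaning of unrestricted, independent assignment; the last assumes a fixed draw of 60.

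The consequence is modest. There is no bias in the allocation, and the power loss is under 2 points at the edge of the 95% range. What remains exposed is any unadjusted between-group comparison at a single time point, where a 10-point imbalance shifts the estimate by 0.05 to 0.15 SD under the assumed sex differences of 0.5 to 1.5 SD, and any comparison by sex, which loses some precision. The change is worth making because it costs almost nothing and can only be made before allocation. The Discussion describes the study as still to be carried out.

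**What to change.** In Section 2.4, replace simple randomisation with 1:1 permuted-block randomisation stratified by sex, with block sizes concealed from those who enrol. Constrain each sex list to close at 30/30. Blocks of 4 and 6 mixed freely at random need not end at 60, so fix how many of each are used: six blocks of 4 and six of 6 in random order give 24 + 36 = 60. The arms are then 60/60 with 30 women and 30 men in each, as Section 2.3 implies, provided that recruitment reaches 60 of each sex. If it falls short, the imbalance within a sex is at most half of the last block.

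In Section 2.9, add sex as a fixed effect in the mixed model, to match the stratification, and make sex a definite covariate in the ANCOVA.

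If simple randomisation is kept, restate 60 per arm in Section 2.3 as the expected size. If a fixed draw of 60 was meant, say so in place of the word simple.

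The cost is two lists instead of one and one extra model term, with no additional participants or staff.

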### 2.6. Health and Safety Protocol

To safeguard the well-being of participants throughout the study, a comprehensive set of risk prevention and control measures will be established, as outlined below. Initially, each participant will undergo a thorough assessment conducted by a qualified physician professional prior to commencing the sports program. This evaluation will include a detailed medical history, a physical examination, and essential tests aimed at identifying any potential cardiovascular, respiratory, or musculoskeletal conditions that could potentially constitute a risk during physical activities.

During each session, constant supervision will be maintained. A certified sports science will lead the group, supported by an assistant trained in first aid. Continuous communication with participants will be prioritized to monitor their well-being, with particular attention given to any signs of fatigue or discomfort that may arise.

In terms of emergency protocols, well-defined procedures will be established to address potential incidents, such as falls, injuries, or cardiovascular distress. The team will be equipped with a first aid kit and will have a pre-established plan for promptly contacting emergency medical services when necessary. Regular breaks will be incorporated into the physical activities to prevent overload and excessive fatigue. Special emphasis will be placed on hydration and appropriate attire. Hydration breaks will be scheduled, and participants will be advised to wear suitable clothing and footwear for the activities. They will also be encouraged to refrain from exercising in extreme heat (above 30 °C) or when experiencing fatigue.

Before each session, brief educational talks will be conducted to raise awareness about the importance of listening to one’s body, recognizing signs of exhaustion or pain, and understanding the necessity of halting activity in the presence of discomfort. Additionally, an incident reporting and tracking system will be implemented to ensure that any incidents or injuries are documented and promptly communicated to the study managers. Participants who experience any mishaps will receive follow-up care to assess their health status and facilitate proper recovery. This proactive approach aims to create a safe and supportive environment for all participants, thereby enhancing the overall effectiveness and integrity of the study.

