## Figures and Tables

**Figure 1 sports-13-00149-f001:**
[figure not shown]
Consort flow gram.

**Table 1 sports-13-00149-t001:** Example of a weekly schedule for the walking football program.

Months	Phases	Weeks	Tests	OMNI *
1	General	1	Basal	3
		2		3
		3		3
		4		3
2		5		4
		6		4
		7		4
		8		4
3		9		5
		10		5
		11		5
		12	Intermediate	5
4	Guided	13		6
		14		6
		15		6
		16		6
5		17		7
		18		7
		19		7
		20		7
6		21		8
		22		8
		23		8
		24	Final	8

* OMNI: Ratio perceived exertion scale, 0 to 10.

**Table 2 sports-13-00149-t002:** Structure of a walking football session.

Phase of the Session	Duration (Minutes)
General warm-up	5
Specific warm-up	5
Main part	45
Cooldown	5

**Table 3 sports-13-00149-t003:** Summary of the test battery.

Type	System	Variables	Test	Reference
Physiologic	Morphology	Body composition	Bioimpedance	[58]
	Morphology	Anthropometry	Height	[58]
Physical	Muscular	MVIC	Hand Grip	[59]
	Muscular	Lower limb strength	Chair Sit to Stand	[60]
	Cardiorespiratory	Aerobic endurance	6 Minute Walk	[60]
	Muscular	Walking speed	Brisk Walk	[61,62]
	Muscular	Range of motion	Chair Seat and Reach	[63]
Questionaries	Physical and mental	Quality of life	15D	[64]
	Physical and mental	Quality of life	SF-12	[65]
	Mental	Mood	Happiness scale	[66]

MVIC: Maximum Voluntary Isometric Contraction.

**Table 4 sports-13-00149-t004:** Comparative summary of tests already used in the walking football literature.

Type	Variables	Test	Has the Test Been Utilised?	Reference
Physiologic	Body composition	Bioimpedance	Yes	[42,87]
	Anthropometry	Height	Yes	[42,87]
Physical	MVIC	Hand Grip	Yes	[56,87,88]
	Lower limb strength	Chair Sit to Stand	Yes	[56]
	Aerobic endurance	6 Minute Walk	Yes	[87]
	Walking speed	Brisk Walk	Yes	[61,62]
	Range of motion	Chair Seat and Reach	No	-
Questionaries	Quality of life	15D	No	-
	Quality of life	SF-12	No	-
	Mood	Happiness scale	No	-

MVIC: Maximum Voluntary Isometric Contraction.

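### Blinding covers only the analysis, so it cannot make the 3- and 6-month effort tests objective as section 2.4 claims, and baseline is timed to programme start rather than to randomisation

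*Protocol article*

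**What the plan says.** Section 2.4 of the protocol article sets the scope of blinding: "during the data analysis phase, researchers will remain blinded to the group allocations". The purpose follows: "This blinding process is crucial for minimizing bias and ensuring that the outcomes are evaluated objectively". The safeguard for allocation is confidentiality: "The details of the group assignments will be securely stored in a password-protected file". The section does not say who may open that file or when participants and staff learn the allocation.

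Section 2.1 lists the assessments as "baseline (prior to the intervention), mid-intervention (at three months), and post-intervention", and section 2.8 also puts the first one before the intervention begins. Table 1, captioned "Example of a weekly schedule for the walking football program", marks the Basal tests in the week 1 row, the Intermediate tests in week 12 and the Final tests in week 24.

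On medical screening, section 2.6 says that "each participant will undergo a thorough assessment conducted by a qualified physician professional prior to commencing the sports program".

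The abstract names strength, endurance, quality of life and happiness among the primary outcomes. Under section 2.7 the control group carries on with ordinary life and is offered the programme after the study.

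**The concern.** Participants play football or do not, so they know their arm throughout follow-up. Protection of the measured outcomes therefore depends on who does the measuring and what they know. The plan is silent on that and assigns the job to analyst blinding.

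Grip strength, the 30-second chair stand, the 6-minute walk and the 30 m brisk walk all respond to how hard a participant tries and how a tester urges them on. If the testers know the arm, or are the people who coached the participant for months, the recorded values can differ between arms without any difference in fitness.

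A second issue concerns baseline. It is timed relative to the programme and not to randomisation. If it is taken after participants learn their arm, the starting values may already reflect that knowledge. Those values enter both analyses in section 2.9: as the first time point of the mixed model and as the ANCOVA covariate.

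**Working it through.** **Step 1: the claim against the mechanism.** Bias of this kind arises when the value is recorded. Analyst blinding acts later, on the recorded data set. It can limit selective modelling or data handling, but it cannot undo a shift already in the data. The claim in section 2.4 that outcomes are thereby evaluated objectively does not follow.

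**Step 2: which outcomes are exposed at 3 and 6 months.**

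| Outcome | Source of exposure | Can a tester be masked? |
|---|---|---|
| Grip, chair stand, 6-minute walk, brisk walk | Effort and encouragement | Yes, imperfectly |
| 15D, SF-12, happiness scale | Participant knows own arm | No |
| Bioimpedance | Does not depend on effort | Little at stake here |

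**Step 3: is there any separation of roles?** Section 2.6 describes the session leader and an assistant. Section 2.8 describes the tests without saying who runs them. Section 2.7 uses Brisk Walk results to balance the teams, so at least one test result reaches session delivery. No section keeps the two roles apart.

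**Step 4: baseline timing.** Sections 2.1 and 2.8 say before the intervention. Table 1 shows week 1. The two can agree if testing comes just before the first session. Even then, members of the experimental group must be told their arm before they attend, so testing before the intervention does not guarantee testing before allocation is known. No section of the text states the order of baseline and randomisation.

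**Step 5: what an unmasked shift could do (illustration).** The plan gives no figure to reproduce on this point.

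- From section 2.9: a 5% significance level, taken here as two-sided.
- From section 2.3: 60 per arm and about 25% loss, so 120 × 0.75 = 90 in all, or 45 per arm.
- Assumed: no true effect, and a measurement shift of *b* SD in favour of one arm.

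For a simple two-group comparison, SE = √(2/n) in SD units. This is √(2/60) = 0.183 with 60 per arm and √(2/45) = 0.211 with 45 per arm.

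False-positive rate = 1 − Φ(1.96 − b/SE) + Φ(−1.96 − b/SE).

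| Assumed shift *b* (SD) | 60 per arm | 45 per arm |
|---|---|---|
| 0 | 5.0% | 5.0% |
| 0.1 | 8.5% | 7.6% |
| 0.2 | 19.5% | 15.8% |
| 0.3 | 37.6% | 29.6% |

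As an example, with b = 0.2 and n = 45, b/SE = 0.2/0.211 = 0.95. The rate is then 1 − Φ(1.01) + Φ(−2.91) ≈ 0.158. Blinding the analyst changes none of these rows.

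**The case against.** The strongest reply is that this is a condensed article. Tester rosters and scripted instructions usually sit in the full protocol, so silence about them is not an error. That is fair, and silence alone would not be a finding. What stands is that the article does state the scope of blinding and draws from it a conclusion that it cannot support.

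It can also be said that the sequence is generated by someone not directly involved in the trial and that the assignments are kept confidential. Both help, but neither says what the testers know at 3 and 6 months.

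On baseline, the reply is largely right. A reader might infer from Table 1 that baseline certainly follows allocation. The documents do not support that: two sections put baseline before the intervention, the table is only an example, its week 1 entry may mark the start of that week, and the flow diagram in Figure 1, which might show the order, is not available here. Baseline after allocation is possible under the wording, not a stated plan.

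A reader might also infer from section 2.6 that only experimental-group members are medically screened, and so could be removed after allocation, because controls start the programme only after the study. That does not hold either. The sentence covers every participant, section 2.5 makes freedom from contraindication to exercise an entry criterion for all, and section 2.9 keeps all randomised participants in the intention-to-treat analysis.

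Finally, some exposure is inherent in the design. No change will mask the self-reports.

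**Conclusion.** The point holds in a limited form. Section 2.4 restricts blinding to the analysis and overstates what that achieves. The effort tests at 3 and 6 months are unprotected on the text as written, and this part does not depend on how baseline is timed. The baseline part is weaker: the wording allows testing with allocation known and needs clarifying, but does not show that this will happen.

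The size of any bias cannot be derived from the documents. The range of about 8% to 30% false positives with 45 per arm rests on an assumed shift of 0.1 to 0.3 SD, no true effect and an unadjusted two-group comparison. It shows why the matter deserves attention and is not an estimate for this trial. The change is cheap and should be made.

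**What to change.** 1. Complete physician screening, baseline tests and questionnaires for all participants before allocation is released, and say so in sections 2.4, 2.6 and 2.8. Show the Basal entry before week 1 in Table 1.
2. State that the 3- and 6-month physical tests are run by existing team members who do not deliver sessions and cannot open the allocation file. They should use one scripted set of instructions, and participants should be asked not to disclose their arm.
3. Reword section 2.4 so that the claim covers only the analysis, and acknowledge that the 15D, SF-12 and happiness answers cannot be masked.

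This needs no extra participants or equipment. The cost is a fixed order of steps before allocation and less flexible rostering. Masking will be imperfect because some participants will reveal their arm.
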